### Outcomes

#### Primary outcome

The primary outcome is the conversion to AD dementia within 3 years of follow-up after the diagnosis of MCI. Visits to assess the study outcome are planned every 6 months. Follow-up time starts at the date of neuropsychological evaluation at baseline and ends at (i) date of conversion, (ii) end of follow-up, (iii) death and (iv) loss to follow-up, whichever occurs first. The conversion to dementia will be diagnosed by specialists according to the American Psychiatric Association’s Diagnostic and Statistical Manual of Mental Disorders, Fifth Edition (DSM-5) on the basis of clinical, cognitive and functional examination, including the CDR. The diagnosis will not be performed based on any of the biomarkers under study as clinicians are blinded with respect to the biomarkers evaluation which is a necessary condition to correctly evaluate the predictive performance of biomarkers and avoid biased estimation of the association between predictors and outcome. Conversion to Alzheimer’s disease is confirmed when an individual receives two consecutive diagnoses of the same type. The date of the first diagnosis will be considered as the date of conversion.

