#### Secondary outcome

The secondary outcomes are the conversion to Alzheimer’s disease within 3 years of follow-up in amnesic patients and the conversion to other forms of dementia.

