For CSF biomarkers, p-tau, t-tau, Aβ1-42, Aβ_1-42/1–40_ ratio and Aβ_1-42_ /p-tau ratio will be evaluated separately. The cut-offs used for each biomarker are reported in Table 3 along with the literature references [28–31]. For the EEG, the classification of results into normal or abnormal based on the SW values will be performed by the expert centre using a machine learning (ML) method based on fine Gaussian support vector machine. This ML classification model has been trained on external data including both healthy individuals and individuals with AD [32] and will be applied to the study cohort. The FDG-PET result will be categorised as either positive or negative by the evaluators at the expert centre based on the methodology previously described [10, 11]. In the case of FDG-PET positivity, it will also be specified whether it is indicative of an AD-like form or other forms of dementia. The APOE-e4 genotype will be classified as none, one (heterozygosis), or both alleles (homozygosis) (see Table 3 and Additional file 3 for details of the cut-offs and literature references).

**Table 3 Tab3:** Reference value for identifying abnormal values by biomarkers

Biomarker	Reference value for categorisation	Literature and notes
**MMSE**	Age- and sex-adjusted score < 24	Applied correction factors from Measso et al. [26] for age ≤ 64 and Magni et al. [25] for age > 64
**DFR**	Age-adjusted score ≤ 6.31	Frasson et al. 2011 [27]
**Hippocampal volume**	< 5° percentile of the normative population	De Francesco et al. 2021 [12]; see Additional file 3

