#### Sensitivity analysis

As sensitivity, the robustness of the stepwise procedure for the selection of variables in the final model will be performed by repeating the stepwise selection considering different levels of p for removal and for re-admission and using the Akaike information criterion (*p* ≤ 0.157). Additionally, the least absolute shrinkage and selection operator (LASSO) method will be used, and the tuning parameter lambda will be chosen by tenfold cross-validation. The predictive performance of the models will be compared.

A complete case analysis will be performed for the final model if the number of missing data will be contained.

Additionally, the competing risk analysis will be performed taking into account death as a competing event using Fine and Gray’s semiparametric proportional sub-distribution hazards model.

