### Model presentation and risk groups

For each predictive model, the hazard ratios with 95%CI and *p*-value will be reported. For the final predictive model, a nomogram will be generated. A nomogram is a graphical representation of the statistical predictive model. It is a visual tool that translates model numeric results into a visual format, making it easier to estimate an outcome based on multiple variables. Each variable occurrence is assigned a specific score based on its contribution to the overall prediction. The total score from all variables is then used to estimate the probability of the predicted event (in this case, the conversion to AD at 3 years) conditioning to the individual characteristics [45]. For this purpose, the covariates in the Cox model will be centred. Sensitivity and specificity corresponding to different thresholds of the prediction risk score will also be provided for the final model. Finally, three or more risk categories will be proposed defining low-, medium- and high-risk groups based on the predictive risk score considering the highest sensitivity corresponding to an adequate level of specificity. This category definition will help the clinician with the choice to treat individuals with MCI based on the likelihood of converting to dementia in the following 3 years. Because avoiding the clinical consequence of treating a false positive is a target as important as treating a true positive, a rate of false positives less than 20% (i.e. specificity of at least 80%) is considered acceptable for a medium–high-risk group. We will start by inspecting deciles of the predictive score and grouping them into homogeneous classes based on levels of sensitivity and specificity. Kaplan–Meier curves will be presented for each risk group.

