#### Analysis of secondary clinical endpoints

For secondary clinical endpoints, conversion to AD in amnesic patients and conversion to other forms of dementia, univariate analysis will be repeated. The final multivariable predictive model identified in the primary analysis will be applied. The model performance will be assessed by Harrel’s C-index, as well as the other performance measures specified in the primary analysis.

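### The nomogram's 3-year AD probability comes from a Cox model that censors death, and the plan does not say whether a non-AD dementia ends follow-up

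*SAP article*

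**What the plan says.** - **Event.** Under Primary outcome: "The primary outcome is the conversion to AD dementia within 3 years of follow-up after the diagnosis of MCI".
- **End of follow-up.** The same section says that follow-up "ends at (i) date of conversion, (ii) end of follow-up, (iii) death and (iv) loss to follow-up, whichever occurs first". A death before conversion is therefore a censored time in the primary Cox model. The section speaks of conversion to dementia in one place and to Alzheimer's disease in another, and does not say which of the two stops the clock. The confirmation rule is worded for AD: "Conversion to Alzheimer’s disease is confirmed when an individual receives two consecutive diagnoses of the same type".
- **Other dementias.** They are expected. Secondary outcome lists "the conversion to other forms of dementia". Under Statistical analysis method, a positive FDG-PET is split further: "it will also be specified whether it is indicative of an AD-like form or other forms of dementia".
- **Competing risks.** Sensitivity analysis is the only place: "the competing risk analysis will be performed taking into account death as a competing event", by a Fine-Gray model. Nothing links that model to the nomogram, calibration or risk-group display.
- **Product.** Under Model presentation and risk groups, the nomogram's total score is used to "estimate the probability of the predicted event (in this case, the conversion to AD at 3 years", given the individual's characteristics. Risk groups are displayed with Kaplan-Meier curves.
- **Secondary endpoints.** Amnesic patients and non-AD dementia are handled together: "The final multivariable predictive model identified in the primary analysis will be applied".

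**The concern.** A Cox model that censors competing events estimates the cause-specific hazard properly. Converting that hazard directly into a 3-year probability, however, answers a hypothetical question: what the AD risk would be if the censored events could not happen. The result is at least as large as the probability a patient actually faces. The same holds for one minus Kaplan-Meier.

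This matters because an absolute risk is the deliverable. The article intends the nomogram to help decide who is eligible for drugs that its Background describes as expensive and with non-negligible adverse effects. It also treats avoiding false positives as no less important than finding true ones.

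The silence on non-AD dementia adds a second problem. Two analysts following this text could reasonably treat a patient diagnosed with another dementia in different ways and obtain different nomograms from the same data.

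**Working it through.** **Inputs from the article (Sample size section).** AD incidence is 40% at 3 years, with a range of 27 to 40% in Table 2. The article states no figure for the quantity disputed here, so there is none to reproduce.

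**Assumptions.** The article gives no rates for the competing events. I take 3-year incidences of 5 to 15% for other dementia and 2 to 5% for death, with constant hazards.

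**Formulas.** Let F_AD, F_O and F_D be the true 3-year cumulative incidences and F their sum.

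- Total hazard: h = −ln(1 − F)/3. Each cause-specific hazard is its share of h, for example h_AD = (F_AD/F)·h.
- Reading A, death and non-AD dementia both censored: 1 − exp(−3·h_AD).
- Reading B, non-AD converters kept at risk to month 36 and only death censored: [h_AD/(h_AD + h_O)]·[1 − exp(−3(h_AD + h_O))].

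**Worked case: AD 40%, other 10%, death 5%.**

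- h = −ln(0.45)/3 = 0.2662; h_AD = (0.40/0.55)·0.2662 = 0.1936; h_O = (0.10/0.55)·0.2662 = 0.0484.
- Reading A: 1 − exp(−0.5807) = 44.1%, an excess of 4.1 points (×1.10).
- Reading B: 0.8·[1 − exp(−0.7259)] = 41.3%, an excess of 1.3 points.

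**Range.**

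| True AD | Other | Death | Reading A | Reading B |
|---|---|---|---|---|
| 27% | 5% | 2% | 28.1% (+1.1, ×1.04) | 27.3% (+0.3) |
| 27% | 15% | 5% | 30.6% (+3.6, ×1.13) | 27.8% (+0.8) |
| 40% | 5% | 2% | 41.7% (+1.7, ×1.04) | 40.5% (+0.5) |
| 40% | 15% | 5% | 45.7% (+5.7, ×1.14) | 41.3% (+1.3) |

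**Illustrative profiles heading to another dementia (all rates assumed).**

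| True AD | Other | Death | Reading A | Reading B |
|---|---|---|---|---|
| 20% | 30% | 3% | 24.8% (+4.8, ×1.24) | 20.4% (+0.4) |
| 10% | 40% | 3% | 13.3% (+3.3, ×1.33) | 10.2% (+0.2) |
| 5% | 60% | 5% | 8.2% (+3.2, ×1.65) | 5.2% (+0.2) |

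In these profiles the relative excess is large, but the excess in points is similar to that for the whole cohort at 40% incidence.

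**Simulation check (400,000 subjects).** For 40/10/5 the simulated true risk was 39.9%, Reading A 44.0% and Reading B 41.2%. For 10/40/3 the figures were 10.0%, 13.3% and 10.2%. Both agree with the formulas.

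**Non-AD endpoint.** Here AD conversion is the main competing event. In the 40/10/5 case, censoring AD and death would give 1 − exp(−3·0.0484) = 13.5% for a true 10%. The plan does not say how AD conversion is handled for this endpoint.

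**The case against.** The strongest objection concerns non-AD dementia. A reader might infer that the plan censors these patients and so overstates AD risk most of all in them. The text does not say so. If the date of conversion means AD conversion only, they stay in the risk set to month 36, which acts like a subdistribution risk set, and only the death component remains. This stands, and it is why the larger range is conditional. Reading B does, however, require that these patients actually be followed to month 36. Any who leave after diagnosis are censored as lost to follow-up, and that part of the bias returns. Even under Reading A, *most of all* holds only in relative terms.

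A much larger figure is also tempting. An AD hazard of 0.170 per year (40% by Kaplan-Meier at 3 years) with a competing hazard of 0.30 gives a true risk of 27.4%, a gap of 12.6 points. But this combines a non-AD profile with the cohort-average AD hazard. FDG-PET pattern is itself a candidate predictor, so the model could give such a patient a lower AD hazard.

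Three further limits stand:

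- **Calibration.** A reader might infer that calibration would share the bias and hide it. Predictive performance speaks only of an observed outcome proportion and names no estimator; Kaplan-Meier is specified only for the risk-group curves.
- **Risk groups.** They are built from deciles of the score using sensitivity and specificity, not from fixed absolute-risk cut-offs. A general upward shift leaves membership unchanged; only competing risk that differs between patients could reorder them, and that has not been quantified.
- **Death.** The planned Fine-Gray analysis addresses it, and at the assumed rates its effect is about one point.

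None of this removes the mismatch: the primary model censors death, and its output is presented as an actual 3-year probability.

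**Conclusion.** The concern holds in a conditional form. The plan presents an absolute AD risk from a model that censors at least one competing event, limits its competing-risk analysis to death in a sensitivity analysis, and leaves the handling of non-AD conversion undefined.

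The overstatement is small if death alone is censored and moderate if non-AD dementia is censored as well, when it is proportionally larger for patients heading to another dementia. Both sizes depend on the assumed event rates and on constant hazards. The estimated biomarker effects, read as cause-specific hazard ratios, are not in question. What is affected is the absolute probability and whatever is computed from it: the nomogram scale, the Brier score and calibration. The Kaplan-Meier risk-group curves have the same weakness.

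**What to change.** 1. In Primary outcome, state that the date of conversion for the primary outcome means AD conversion. Define non-AD dementia and death without dementia as competing events, each with a dating rule.
2. Keep the Cox model for cause-specific biomarker effects.
3. Derive the 3-year AD probability for the nomogram, Brier score and calibration from cumulative incidence. Use either a Fine-Gray model with both competing events or combined cause-specific models.
4. Use Aalen-Johansen estimates for observed risk in calibration and in place of the Kaplan-Meier risk-group curves.
5. For the non-AD endpoint, treat AD conversion as a competing event.

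**Cost.** SAP wording and modest programming, with no new data collection, since non-AD conversion is already a secondary outcome. Predicted risks become slightly lower.

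The combined cause-specific option is limited by sparse events. At an assumed 5 to 10% incidence, 400 patients yield 20 to 40 events per competing cause. At the plan's own 9.5 events per parameter, that supports 20/9.5 ≈ 2 to 40/9.5 ≈ 4 parameters. Those models must stay small, which favours the Fine-Gray route.

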### Model presentation and risk groups

For each predictive model, the hazard ratios with 95%CI and *p*-value will be reported. For the final predictive model, a nomogram will be generated. A nomogram is a graphical representation of the statistical predictive model. It is a visual tool that translates model numeric results into a visual format, making it easier to estimate an outcome based on multiple variables. Each variable occurrence is assigned a specific score based on its contribution to the overall prediction. The total score from all variables is then used to estimate the probability of the predicted event (in this case, the conversion to AD at 3 years) conditioning to the individual characteristics [45]. For this purpose, the covariates in the Cox model will be centred. Sensitivity and specificity corresponding to different thresholds of the prediction risk score will also be provided for the final model. Finally, three or more risk categories will be proposed defining low-, medium- and high-risk groups based on the predictive risk score considering the highest sensitivity corresponding to an adequate level of specificity. This category definition will help the clinician with the choice to treat individuals with MCI based on the likelihood of converting to dementia in the following 3 years. Because avoiding the clinical consequence of treating a false positive is a target as important as treating a true positive, a rate of false positives less than 20% (i.e. specificity of at least 80%) is considered acceptable for a medium–high-risk group. We will start by inspecting deciles of the predictive score and grouping them into homogeneous classes based on levels of sensitivity and specificity. Kaplan–Meier curves will be presented for each risk group.

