#### Statistical model and variable selection

Initially, an analysis of socio-demographic and clinical variables will be conducted using the Cox model to identify a core of variables significantly associated with the outcome that will be included in the development of the prognostic multivariable model. A check of multicollinearity between predictors will be assessed, then a stepwise selection starting from the full model will be applied using a threshold of 0.10 for removal and 0.05 for re-admission of variables. A final check of variables not selected by stepwise will be conducted using the likelihood ratio test [36, 37]. Age and sex will be forced in the procedure selection and retained in the final model. Subsequently, these selected variables will be included in multivariable models with the addition of individual biomarkers one at a time. The additional predictive value of each biomarker beyond clinical and socio-demographic variables will be calculated. The performance results will be used to determine for each biomarker which form (continuous or categorical) will be chosen for the development of the multivariable prediction model. Categorisation is typically preferred for the application in clinical practice, but as any categorisation implies a loss of information, we will select the biomarker in a categorical form if the loss in performance could be considered negligible with respect to the continuous form. Categorisation will also be chosen in cases where non-linearity is detected for the continuous form. The categorisation according to the threshold provided by the experts (Table 3) will be preferred in case a small loss of performance is observed compared to the continuous form.

The final predictive model will be identified through a multivariable model considering as eligible predictors all the biomarkers and all selected predictors among the clinical and socio-demographic variables using the stepwise selection procedure as described above. Age and sex will be forced into the model selection process. A final check of the result from the automatic selection procedure will be conducted to ensure that no significant biomarkers were excluded and, vice versa, that no negligible biomarkers were included.

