#### Internal validation

The final predictive model will be internally validated using the bootstrap technique with 500 bootstrap samples [38]. The stepwise selection will be repeated in the validation process (i.e. stepwise procedure will be repeated within each bootstrap sample). Consequently, Harrel’s c-index of the predictive model will be adjusted to take into account the estimated potential overfitting and a corrected c-index will be reported. Apparent and corrected calibration measures will be reported [44]. The correction will be performed using the shrinkage factor calculated with bootstrapping. The shrinkage factor may take values between 0 and 1, and a value above 0.90 indicates a small overfitting. As the shrinkage of regression coefficients is an important way to reduce overfitting, the shrinkage factor will be also applied to regression coefficients and intercept of the final model [38] to improve the prediction ability of the regression model when applied to external data. Both the original and shrunken regression coefficients will be reported.

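### The final model's hazard ratios, 95% CIs and p-values are reported without any qualification for the stepwise selection, so they are too optimistic for weak or null markers that happen to be retained

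*SAP article*

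**What the plan says.** Under Statistical model and variable selection, the clinical and socio-demographic core is chosen by stepwise selection from the full model, "using a threshold of 0.10 for removal and 0.05 for re-admission of variables". The final model takes all biomarkers and the selected clinical variables as candidates, "using the stepwise selection procedure as described above". Two variables escape the rule: "Age and sex will be forced into the model selection process". Two further steps look at the same data. The form of each biomarker is settled beforehand ("The performance results will be used to determine for each biomarker which form (continuous or categorical) will be chosen"), and afterwards a check is made that "no significant biomarkers were excluded and, vice versa, that no negligible biomarkers were included".

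Under Model presentation and risk groups, "For each predictive model, the hazard ratios with 95%CI and" p-value are to be reported, with no remark on how the variables came to be in the model.

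Under Internal validation, the stepwise procedure is repeated in each of 500 bootstrap samples. The output serves a corrected c-index, corrected calibration and a shrinkage factor for the coefficients; "Both the original and shrunken regression coefficients will be reported". Under Sensitivity analysis, the selection rule is varied (other p thresholds, AIC, LASSO) and the resulting models are compared on predictive performance. None of these sections mentions the CIs or p-values of selected variables.

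**The concern.** A non-forced variable appears in the final table only because its estimate in these data was large enough to survive the 0.10 rule. An ordinary CI and p-value take the set of variables as given and ignore that condition. Among retained variables, estimates are therefore pushed away from HR 1 and intervals cover the truth less often than 95%. The effect is largest where the true effect is smallest.

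This would matter less if the article sought prediction only. Its Study objectives section, however, also asks the model to single out the biomarkers that predict conversion, and the Introduction ties the result to eligibility for treatment. Readers will look to the final HR table to see which markers carry evidence. A marker with little or no real contribution could appear there with an interval clear of 1.

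**Working it through.** **The plan's own figures.** The article gives no figure for coverage after selection. Its nearest relevant figure is the limit of 17 candidate predictors, which reproduces if the target shrinkage is 0.90 (my assumption; not stated). Subjects per parameter are 1/[(0.90 − 1) × ln(1 − 0.31/0.90)] = 23.68. Multiplied by 0.16 × 2.5, this gives 9.47, about 9.5 events per parameter. With 400 × 40% = 160 events, 160/9.5 = 16.8, about 17. The AIC threshold also reproduces: P(χ² with 1 df > 2) = 0.157.

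**Inputs.** Removal at p 0.10 means that a variable stays if |Z| > c = 1.645. The 95% CI is the estimate ± 1.96 SE. Let θ be the expected z, that is, the true log HR divided by its SE. I treat one predictor with a normal estimate, Z ~ N(θ, 1).

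**Formulas.**
- P(retained) = P(|Z| > c)
- Coverage given retention = P(|Z − θ| < 1.96 and |Z| > c) / P(retained)
- Inflation = mean retained Z / θ = 1 + [φ(c − θ) − φ(c + θ)] / [θ × P(retained)]

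At θ = 0 coverage is (0.10 − 0.05)/0.10 = 50%, whatever the sample size. At θ = 0.5 it is [Φ(1.96) − Φ(1.145)]/0.142 = 0.101/0.142 = 71%.

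| Expected z | P(retained) | Coverage given retention | Mean retained log HR / truth |
|---|---|---|---|
| 0 | 0.100 | 50% | – |
| 0.5 | 0.142 | 71% | 3.35 |
| 1 | 0.264 | 89% | 2.18 |
| 1.5 | 0.443 | 94% | not computed |
| 2 | 0.639 | 96% | 1.29 |
| 3 | 0.912 | 97% | not computed |

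**Scale.** Take a 50/50 binary marker with no effect and the planned 160 events. The SE is 1/√(160 × 0.25) = 0.158. If it is retained, its mean |z| is 2φ(1.645)/0.10 = 2.06, an apparent HR of about exp(2.06 × 0.158) = 1.39, or its inverse.

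**Check with the actual procedure.** Stepwise Cox selection was simulated from the full model (removal 0.10, re-admission 0.05) with 17 candidates: 2 forced, 5 real, 10 null. There were 350–400 subjects and 400 runs per scenario. Effect sizes, correlations and censoring are assumptions. Among retained null variables, the share with p < 0.05 was 50.1% with uncorrelated predictors and 58.6%, 58.5% and 58.7% at pairwise correlation 0.3, 0.5 and 0.7 (SE about 2 points). Between 11.5% and 13.6% of null candidates were retained. The one-predictor figure of 50% is therefore not an exaggeration for the multivariable procedure.

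**Does shrinkage repair it?** A common factor s leaves the Wald statistic unchanged if the SE is scaled with the coefficient: sβ/(s·SE) = β/SE. Nor can it undo uneven inflation. At the 0.90 that the article treats as the mark of small overfitting, 3.35, 2.18 and 1.29 become 3.0, 2.0 and 1.2.

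**The case against.** The strongest reply is that this is a prediction study. Decisions rest on the predicted risk, the nomogram and the risk groups, and the HR table merely describes the fitted model. Optimism from selection is handled where it affects prediction: the stepwise procedure is repeated in the bootstrap, the c-index and calibration are corrected, and the coefficients are shrunk. Every biomarker, retained or not, is also reported singly (accuracy measures and univariate Cox model) and as an addition to the clinical core (likelihood ratio test, change in c-statistic, NRI). The candidates were chosen on published evidence, so a marker with exactly no effect is not the typical case. Without conditioning on retention, a null variable gets an interval excluding 1 in about 0.10 × 0.50 = 5% of studies.

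Most of this stands, and it limits the point. It does not remove it. The one-at-a-time results do not show which biomarkers contribute jointly; they also rest on a selected clinical core and a data-driven choice of form. The table readers will see is conditional on retention. In the simulation the unconditional rate ran from 0.115 × 0.501 = 5.8% to 0.136 × 0.587 = 8.0%.

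A reader might infer that the final table's intervals are wrong half the time across the board, or that the prediction model itself is invalid. The documents support neither. The 50% belongs to an exactly null, non-forced variable that has been retained under the 0.10 rule; under the AIC rule (p ≤ 0.157) the share excluding 1 would be 0.05/0.157 = 32%.

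**Conclusion.** The concern holds as a defect of reporting. The selected model's CIs and p-values are given without adjustment or caveat, and for weak or null retained markers they are too optimistic. Coverage given retention is about 50%, 71% and 89% at expected z of 0, 0.5 and 1, with log HRs inflated about 3.4-fold and 2.2-fold at 0.5 and 1. From expected z of 1.5 to 3 coverage is 94–97%. Age and sex are forced and lie outside the rule. Predictions and risk groups are not affected.

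The figures rest on a one-predictor normal approximation and on the removal test agreeing with the Wald test. That the intervals are the ordinary ones is inferred from the absence of any adjustment; the article does not say so. The data-driven choice of form and the ROC-derived cut-offs were not modelled and would be expected to make matters worse.

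**What to change.** Under Model presentation and risk groups:

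1. State that the CIs and p-values of the selected model are conditional on the selection and are not valid as tests of individual biomarkers.
2. Print beside them the HRs and 95% CIs of the full model from before selection. Clinical variables that have already passed the first stepwise round should be marked as such, or the full model should contain all clinical candidates.
3. Add each variable's inclusion frequency over the 500 bootstrap samples that already repeat the stepwise selection.

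Do not replace the main intervals by bootstrap percentile intervals with zeros for samples in which the variable was dropped. Such an interval clears HR 1 only if the observed z exceeds about 1.645 + 1.96 = 3.6. A retained predictor with expected z of 3 would then exclude HR 1 in about [1 − Φ(0.605)]/0.912 = 0.273/0.912 = 30% of cases, against 93% with ordinary intervals.

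The cost is SAP wording, a longer table and less favourable-looking evidence for weak markers; no new data are needed. The full-model intervals still leave out the data-driven choice of biomarker form and cut-off, and the label should say so.

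### The sensitivity and specificity behind the risk groups are left out of the bootstrap correction, so the 80% specificity criterion is judged on optimistic figures

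*SAP article*

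**What the plan says.** Two sections of the SAP article bear on this.

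*Model presentation and risk groups.* The groups are defined "based on the predictive risk score considering the highest sensitivity corresponding to an adequate level of specificity". The working procedure is given as "We will start by inspecting deciles of the predictive score and grouping them into homogeneous classes based on levels of sensitivity and specificity". The standard is that "a rate of false positives less than 20% (i.e. specificity of at least 80%) is considered acceptable for a medium–high-risk group". The section also promises that "Sensitivity and specificity corresponding to different thresholds of the prediction risk score will also be provided for the final model". It mentions no correction for overfitting in any of these figures. The groups are meant to help clinicians decide whom to treat.

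*Internal validation.* The final model is to be "internally validated using the bootstrap technique with 500 bootstrap samples". The step repeated is named: "stepwise procedure will be repeated within each bootstrap sample". The corrected quantities are named too: "a corrected c-index will be reported", apparent and corrected calibration measures are given, and one shrinkage factor is applied to the coefficients and intercept. Sensitivity, specificity and the search for cut-offs are not among them.

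The Discussion adds that external validation is lacking and that the enrolment target of 500 was not reached.

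**The concern.** The same patients select the predictors, supply the coefficients, set the cut-offs and provide the sensitivity and specificity by which those cut-offs are judged. Each step favours the development data. The plan recognises this for the c-index and calibration and corrects both, but the correction stops short of the numbers that define the risk groups.

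Those numbers matter most in use. The plan says that avoiding treatment of a false positive counts as much as treating a true positive, and it expresses this as a limit on the false-positive rate. If the limit is checked against an uncorrected value, the published groups will look somewhat better than they perform. With no external data set, the internal correction is the only safeguard.

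**Working it through.** **1. The plan's own figures.** In Table 2 the half-width for specificity is 1.96·√[Sp(1−Sp) / (N(1−incidence))]. With Sp = 0.80 and N = 400:

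- incidence 27%: 1.96·√(0.16/292) = 4.6%
- incidence 35%: 1.96·√(0.16/260) = 4.9%
- incidence 40%: 1.96·√(0.16/240) = 5.1%

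All 18 cells of Table 2 reproduce. The enrolment figure does too: 400/(1−0.20) = 500.

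For the prediction model, with Cox-Snell R² = 0.31 and a target shrinkage of 0.9 (assumed), patients per parameter are 1/[(0.9−1)·ln(1−0.31/0.9)] = 23.68. Events per parameter are 23.68 × 0.16 × 2.5 = 9.47 (stated 9.5). With 400 × 0.40 = 160 events, 160/9.47 = 16.9, which matches the stated 17 candidates.

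**2. Does the planned shrinkage help?** No. Multiplying every coefficient by one positive factor keeps patients in the same order. A cut-off at a decile or any other quantile of the score then splits the cohort in the same way, so sensitivity and specificity are the same before and after.

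**3. Size of the optimism.** This comes from simulation.

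- From the plan: N = 400; incidence 27%, 35% and 40%; 17 candidates; removal at p > 0.10; two predictors forced in.
- Assumed: independent normal predictors, five of them real, with discrimination in new patients of about 0.79; 30 candidates as a rough count of all listed parameters; a logistic model for a complete 3-year outcome in place of the Cox model; unchanged case mix.
- Incidence of 16% is a low extreme only. In the plan it is a rate, and 0.16 × 2.5 = 0.40.
- Each row has 500 simulated studies. True values come from 120,000 new patients.
- Two rules were tried: the lowest cut-off anywhere on the score with apparent specificity of at least 80% (free), and the lowest decile boundary meeting the same condition.

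Free cut-off (apparent → true):

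| Candidates | Incidence | Specificity % | Sensitivity % | Studies with true specificity < 80% | Same, true model known |
|---|---|---|---|---|---|
| 17 | 16% | 80.1 → 78.8 | 69.1 → 63.5 | 70.0% | 54.0% |
| 17 | 27% | 80.1 → 78.6 | 66.6 → 63.1 | 71.8% | 51.4% |
| 17 | 35% | 80.1 → 78.5 | 66.2 → 63.2 | 71.6% | 54.8% |
| 17 | 40% | 80.2 → 78.2 | 65.8 → 63.2 | 71.8% | 51.2% |
| 30 | 16% | 80.1 → 78.2 | 71.1 → 62.3 | 78.6% | 48.4% |
| 30 | 27% | 80.1 → 77.5 | 68.5 → 63.6 | 84.4% | 60.0% |
| 30 | 35% | 80.2 → 77.3 | 67.7 → 63.3 | 85.2% | 56.2% |
| 30 | 40% | 80.2 → 77.5 | 66.9 → 63.2 | 82.2% | 49.8% |

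Decile boundary (apparent → true):

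| Candidates | Incidence | Specificity % | Sensitivity % | Studies with true specificity < 80% |
|---|---|---|---|---|
| 17 | 16% | 86.7 → 85.5 | 58.9 → 53.3 | 4.4% |
| 17 | 27% | 83.1 → 81.6 | 62.2 → 58.7 | 27.8% |
| 17 | 35% | 85.0 → 83.5 | 58.9 → 55.9 | 6.8% |
| 17 | 40% | 85.0 → 83.2 | 58.6 → 56.0 | 21.8% |
| 30 | 16% | 86.5 → 84.6 | 61.3 → 52.5 | 10.6% |
| 30 | 27% | 83.2 → 80.6 | 64.2 → 59.2 | 40.6% |
| 30 | 35% | 85.1 → 82.4 | 60.2 → 56.1 | 13.0% |
| 30 | 40% | 84.8 → 82.3 | 59.8 → 56.3 | 29.6% |

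At 27–40% incidence, specificity optimism runs from 1.5 points (80.1 − 78.6) to 2.9 (80.2 − 77.3). Sensitivity optimism runs from 2.6 (65.8 − 63.2) to 5.0 (64.2 − 59.2). At 16% with 30 candidates the sensitivity figure reaches 8.8 (71.1 − 62.3). With 351 patients, an assumed shortfall, it reaches 6.4 (68.8 − 62.4) at 27% and 30 candidates. Further runs at N = 400 put the decile failure share at 16–48%.

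**4. Does the remedy work?** The cut-off choice was repeated with the selection in each resample (60 data sets, 50 resamples each, incidence 40%).

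| Rule | Candidates | Apparent | Corrected | True |
|---|---|---|---|---|
| Free | 17 | 80.2 | 77.9 | 78.5 |
| Free | 30 | 80.2 | 76.5 | 77.1 |
| Decile | 17 | 84.6 | 82.4 | 82.9 |
| Decile | 30 | 84.5 | 81.0 | 81.7 |

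The corrected value lies within 0.5 to 0.7 points of the truth.

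**The case against.** A reader might infer that the 80% rule will usually fail in new patients. The documents do not support that. The procedure starts from deciles, and the coarse grid leaves a margin above 80%; failure there was the minority case at N = 400 in every setting. The high failure shares belong to a cut-off tuned to the limit, and much of even that is not overfitting: with the true model known, 48–60% of studies still fall short. Optimism correction adjusts the average and does not remove this sampling error.

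A reader might also take the 80% as a promise. The plan says only that groups will be proposed and that such a rate is acceptable, and it admits that external validation is lacking.

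Three further objections have weight. The average specificity optimism is smaller than the plan's own half-width of 4.6 to 5.1 points. Thirty candidates and independent predictors are assumptions; the plan states 17, and several of its biomarkers overlap. Inspecting and grouping deciles is also a matter of judgement, which no bootstrap can repeat as it stands.

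What remains is this. The optimism is a bias in one direction on top of the random error, so a wide interval does not excuse it. It is present with 17 candidates as well. And the plan only begins with deciles while aiming for the highest sensitivity at adequate specificity, which pulls a finer cut-off towards the limit. How often the rule fails therefore depends on a choice left open until the data are seen.

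**Conclusion.** The point holds in a limited form. As written, the sensitivity and specificity reported for the risk groups, and the check against 80%, use apparent values that neither the bootstrap nor the shrinkage corrects. At N = 400 and 27–40% incidence the expected optimism is modest: roughly 1 to 3 points for specificity and 3 to 5 for sensitivity. A cut-off at the 80% limit would more often than not miss it in new patients (about 70–85% of studies, against 48–60% from sampling error alone). A decile cut-off would miss it in about 4–48%.

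These sizes rest on the simulation assumptions above. Two features of the plan would push the optimism up: the final sample is smaller than planned, and the bootstrap is not said to repeat the ROC-derived biomarker cut-offs or the choice between continuous and categorical forms. Neither of these two data-driven steps was simulated. The plan should be changed, because these groups are the output intended to guide treatment decisions.

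**What to change.** 1. Replace the inspection of deciles with a fixed algorithm, written down before the data are analysed. One example is the lowest decile boundary that meets the plan's own specificity criterion.
2. Run that algorithm together with the variable selection in each of the 500 bootstrap samples. Apply each resulting model and cut-off to the original cohort to estimate the optimism.
3. For each proposed group, report apparent and optimism-corrected sensitivity, specificity and predictive values, with confidence intervals. The intervals are needed because correction does not remove the sampling error of the cut-off.
4. Apply the 80% criterion to the corrected specificity.

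The bootstrap loop already exists, so the cost is a little more code, the work of turning a judgement into a rule, and slightly less favourable reported accuracy. No further data are needed.
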